### Randomization

The central randomization list was generated by an independent statistician using SPSS (version 24.0, IBM, NY, USA). Altogether, 36 patients will be assigned to the intervention group and to the control group using a balanced block randomization with 6 blocks. We will randomly select blocks of size 4. Telephone-based randomization will be performed at each coordinating center by an independent physician who is not engaged in recruitment, treatment, or assessment. Participants will be randomly assigned in each site to the YNF group and the placebo group in a ratio of 1:1. After screening, if the patient agrees to participate and voluntarily signs the informed consent form (Additional file 2), the independent physician in each trial site will sequentially assign a random number to them.

### Blinding

This clinical trial will be double blind. The physicians, investigators, co-investigators, clinical trial pharmacists, and patients are all blinded to the allocation, except for the independent statistician who generated the randomization.

The placebo granules will be indistinguishable from the YNF granules in shape, size, color, and packaging. Thus, all clinicians and participants will be masked. The packaging will be labeled with sequential random numbers in advance by a pharmaceutical company according to the randomization list sent by the independent statistician. The independent statistician will go to the pharmaceutical company to check the packaging when the drugs are being labeled. At each trial site, based on their allocation, a patient will be given the package of YNF or the placebo with the lowest number by a designated clinical trial pharmacist who is not involved with the study and is blind to the allocation.

Unblinding will be done according to the standard operating procedure of the contract research organization [17]. For each subject, an emergency plan and their treatment plan will be sealed in an opaque envelope, to allow unblinding if there is a serious adverse reaction and possibly to ensure the correct treatment method was administered. If an emergency occurs, the principal investigator will ask an independent physician to unblind the patient and the incident will be reported to the independent safety monitoring board.

### Intervention

According to the guideline for the management of ADPKD [18], drugs used in the treatment of hypertension, hematuria, concurrent infections, and other diseases will be used reasonably for patients in both groups as basic therapy, except for Chinese patent drugs. The name and dosage of any drug administered will be recorded. In addition to their standardized Western medicine, participants randomized to the treatment group will be administered YNF as an oral dose of 36 g twice daily 1 h after breakfast and dinner for 24 weeks. Those in the control group will receive the placebo as an oral dose of 36 g twice daily 1 h after breakfast and dinner for 24 weeks. Both groups will receive behavioral intervention and health education, such as diet instructions. All co-investigators and patients will be educated about drug administration methods.

The YNF granules (10% YNF) and the placebo granules will be manufactured by Jiangsu Tianyin Pharmaceutical Co. Ltd. ([name]) according to good manufacturing practice. The composition and action of each herb are summarized in Table 1.

**Table 1 Tab1:** Composition and action of *yinang* formulation in Chinese herbal medicine

Ingredient	Granule dose	Action (TCM)	Pharmaceutical action
Rhizoma sparganii (*sanleng*)	10 g	1. Regulate qi 2. Relieve pain 3. Promote blood circulation 4. Alleviate stagnation	1. Inhibit platelet aggregation and thrombosis
Ranunculus ternatus Thunb (*maozhuacao*)	30 g	1. Dissipate phlegm 2. Dispel stasis 3. Detoxify 4. Detumescence	1. Anti-inflammation 2. Anti-tumor
Spina gleditsiae (*zaojiaoci*)	6 g	1. Detoxify 2. Disperse swelling	1. Anti-tumor
Rhizoma drynariae (*gusuibu*)	10 g	1. Reinforce the kidneys 2. Strengthen bones 3. Relieve pain	1. Prevent osteoporosis 2. Anti-inflammatory
Astragalus (*huangqi*)	30 g	1. Tonify qi 2. Diuresis	1. Improve the immune function 2. Anti-oxidant 3. Increase resistance to radiation 4. Anti-tumor
*Codonopsis pilosula* (*dangshen*)	30 g	1. Invigorate the spleen 2. Replenish qi	1. Regulate the central nervous system 2. Enhance immune function 3. Regulate gastrointestinal motility 4. Cardiovascular protective effect
Angelica sinensis (*danggui*)	10 g	1. Enrich the blood 2. Invigorate the circulation of blood	1. Anti-atherosclerosis 2. Bacteriostasis 3. Anti-hypoxia 4. Regulation of immune function 5. Inhibit platelet aggregation
Paeoniae radix (*chishao*)	15 g	1. Activate blood circulation to dissipate blood stasis	1. Inhibition of platelet and erythrocyte aggregation 2. Anti-atherosclerosis 3. Anti-tumor 4. Protect the heart and liver 5. Anti-coagulation and anti-thrombosis
Radix paeoniae alba (*baishao*)	10 g	1. Nourish the blood 2. Reduce yin 3. Soothe the liver 4. Relieve pain 5. Stabilize yin and yang in the liver	1. Anti-inflammation 2. Pain relief 3. Liver protection
*Duchesnea indica* (*shemei*)	10 g	1. Clear away heat and toxic material 2. Activate blood circulation to dissipate blood stasis	1. Anti-oxidant
Hedyotis diffusa willd (*baihuasheshecao*)	15 g	1. Dissolve phlegm 2. Detoxification 3. Detumescence	1. Anti-inflammation 2. Anti-tumor 3. Regulation of immune function
Cowherb seed (*wangbuliuxing*)	15 g	1. Activate blood circulation to dredge collaterals 2. Detumescence 3. Relieve pain	1. Inhibit microcapillary proliferation 2. Inhibit migration and adhesion of endothelial cells
Semen brassicae (*baijiezi*)	15 g	1. Activate qi 2. Activate blood circulation 3. Dredge collaterals 4. Relieve pain	1. Anti-hepatic fibrosis 2. Regulation of TGF-β1/Smad, NF-κB, and AKT signaling pathways 3. Reduction of extracellular matrix deposition
Plantaginis seeds (*cheqianzi*)	15 g	1. Clear heat 2. Diuresis 3. Permeate dampness 4. Promote circulation 5. Clear eyesight 6. Expectorant	1. Eliminate oxygenic free radicals 2. Anti-oxidation in lipid metabolism 3. Anti-oxidation
*Polygonum cuspidatum* (*huzhang*)	10 g	1. Relieve coughing 2. Resolve phlegm 3. Dispel wind dampness 4. Remove fluid 5. Dissipate blood stasis 6. Relieve pain	1. Anti-bacterial and anti-viral 2. Protect the cardiovascular system 3. Anti-inflammation and analgesic 4. Liver protection 5. Enhance immunity 6. Anti-tumor
*Centella asiatica* (*jixuecao*)	30 g	1. Clear heat 2. Disperse dampness 3. Detoxify 4. Reduce swelling	1. Improve the microcirculation 2. Relieve pain 3. Anti-oxidant 4. Anti-bacterial 5. Anti-inflammation 6. Anti-fibrous tissue proliferation
Prepared rhubarb (*dahuang*)	10 g	1. Alleviate accumulation 2. Clear heat 3. Detoxify 4. Remove blood stasis 5. Dredge meridians	1. Promote defecation 2. Anti-bacterial 3. Protect the liver and gallbladder 4. Lower blood pressure 5. Lower blood lipid levels

*TCM* traditional Chinese medicine

### Measurement items and time points of data collection

Relevant examinations will be performed to collect patient data at 24 weeks before baseline, at baseline, every 4 weeks from 4 to 24 weeks during treatment, and an additional follow-up evaluation will be performed at visit 9 (48 weeks). General information collected will include name, age, gender, ID number, date of birth, home address, contact information, history of present illness, past medical history, family history, personal life history, menstrual history, marital history, allergy history, social history, physical examination results, and laboratory examination results.

There is evidence that age-related TKV can reflect the progress of ADPKD. An MRI scan can accurately measure renal blood flow and evaluate renal cyst compression, which is associated with pain, hypertension, hematuria, albuminuria, and loss of renal function. TKV combined with age and renal function can be used to evaluate the risk of progress to ESRD [19]. The T2 shortening imaging technique of MRI with no radiation damage, no use of gadolinium as a contrast agent, and no risk of nephrogenic systemic fibrosis is recommended and will be used in this study [20]. The outcome is the percentage semi-annual change in TKV measured by MRI, which will be performed at visit 1, visit 2 (24 weeks after visit 1), and visit 8 (24 weeks after visit 2) to observe the growth in kidney volume before and after the intervention.

Items to be measured and the time points of data collection are listed in Table 2.

**Table 2 Tab2:** SPIRIT table: Measurement items and time points of data capture

Items	Screening	Baseline	Treatment						Follow-up
	Visit 1	Visit 2	Visit 3	Visit 4	Visit 5	Visit 6	Visit 7	Visit 8	Visit 9
	−24 weeks	0 weeks	4 weeks	8 weeks	12 weeks	16 weeks	20 weeks	24 weeks	48 weeks
General									
Informed consent	×								
Inclusion and exclusion criteria	×								
Collect general information	×								
General physical examination	×								
Urine hCG (only women)	×								
Medical and drug use history	×								
Concomitant disease and treatment	×								
Combined medication	×	×	×	×	×	×	×	×	×
Effectiveness observation									
Vital signs	×	×	×	×	×	×	×	×	×
TCM symptoms	×	×	×	×	×	×	×	×	×
Pain evaluation	×	×	×	×	×	×	×	×	×
Renal function (eGFR, Scr, BUN)	×	×	×	×	×	×	×	×	×
MRI (TKV)	×	×						×	
Blood electrolytes	×	×			×			×	×
Urine β2-MG, mALB/Cr, RBP	×	×						×	×
Safety observation									
Blood test ^#^	×	×			×			×	×
Urine test	×	×	×	×	×	×	×	×	×
Stool routine and occult blood test	×	×			×			×	×
Liver function (ALT, AST, γ-GT)	×	×			×			×	×
Electrocardiogram	×	×						×	×
Other data									
Adverse events			×	×	×	×	×	×	
Allocation		×							
Drug distribution		×	×	×	×	×	×		
Drug recycling			×	×	×	×	×	×	
Drug count			×	×	×	×	×	×	
Research conclusion								×	×

Each visit allows a window of 3 days

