### Outcomes

The primary outcome of this trial will be the eGFR using the CKD Epidemiology Collaboration formula [21]. Secondary outcomes include changes in TKV, Scr, blood urea nitrogen (BUN), TCM symptoms, and pain. A composite outcome looks at the incidence rates of all possible safety events between two groups. AEs will be monitored throughout the trial and several biological indicators (blood and urine tests, electrocardiograms, and liver function test) will also be closely watched.

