### Statistical analysis

A formal and detailed statistical analysis plan will be formulated before the database is locked. The baseline characteristics of both groups, such as gender, age, and smoking status, will be compared by either a χ^2^ test or Student’s *t*-test. Continuous variables will be presented as means ± standard deviations or medians, and differences in such variables will be analyzed using an independent *t*-test or the Wilcoxon signed-rank test. A repeated measurement of variance analysis model of these outcomes will be built.

The difference in eGFR will be tested using two-way ANOVA with repeated measures. Categorical variables will be expressed as numbers and percentages, and differences in such variables will be calculated and compared using a χ^2^ test and Fisher’s exact test. All statistical tests will be two-sided, and the level of significance will be set to *P* < 0.05. Multiple imputation will be used to handle missing data. All patients enrolled will be included in the primary analysis in accordance with the intention-to-treat principle. The statistical analysis will be performed in a blind manner by an independent statistician using SPSS (version 24.0, IBM, NY, USA). No additional analyses or an interim analysis are scheduled.

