### Trial status

The research strategy and study protocol were developed between October 2017 and June 2019. From October 2018 to July 2019, patients were screened and TKV was measured by MRI 24 weeks before the baseline. The follow-up visits and data analysis will take place from July 2019 to December 2020.

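### The TKV analysis names no covariate and does not say how the pre-treatment (run-in) growth enters the between-arm comparison, so precision may be lost on a secondary outcome

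*Protocol article*

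**What the plan says.** In the protocol article, the section on measurement items and time points defines the TKV endpoint: "The outcome is the percentage semi-annual change in TKV measured by MRI". It schedules three scans, at Visits 1, 2 and 8, each 24 weeks after the one before, with the stated purpose "to observe the growth in kidney volume before and after the intervention". Table 2 labels Visit 1 as screening and Visit 2 as baseline, and places allocation at Visit 2. Both earlier scans therefore precede treatment. The Trial status section confirms the timing: "patients were screened and TKV was measured by MRI 24 weeks before the baseline".

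TKV is a secondary outcome: "Secondary outcomes include changes in TKV, Scr, blood urea nitrogen (BUN), TCM symptoms, and pain".

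For continuous variables, the Statistical analysis section says that "differences in such variables will be analyzed using an independent *t*-test or the Wilcoxon signed-rank test", and adds: "A repeated measurement of variance analysis model of these outcomes will be built". It names no covariate for any outcome and does not say which visits or intervals enter the repeated-measures model for TKV. A detailed SAP is promised before database lock; it is not shown.

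**The concern.** The first two scans give each patient's own growth over the 24 weeks before treatment. Where patients differ persistently in growth rate, that is a natural covariate for growth on treatment. The named methods do not use it that way:

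- An independent t-test of the Visit 2 to Visit 8 change makes no use of Visit 1.
- A repeated-measures ANOVA can include Visit 1, but as a further response and not as a covariate.

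What is at stake is precision. The sample size was set on eGFR alone and no power is stated for TKV. With about 32 to 36 patients per arm, variance that could be removed with data already collected is worth removing.

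**Working it through.** **The plan's own figure.** The only sample size stated is for eGFR: difference 6, SD 8.53, two-sided alpha 0.05, power 0.80, 1:1. Then n per arm = (1.960 + 0.842)² × 8.53² × 2 / 6² = 31.7, so 32 per arm and 64 in total. Allowing for 10% dropout, 64 / 0.9 = 71.1, so 72. This reproduces. There is no corresponding figure for TKV, so 32 per arm is used below.

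**Model.** Work on log TKV. Let true 24-week growth have SD s between patients, let each scan have independent error with SD e, and let p be the correlation between true growth in the two periods (persistence). The run-in change and the on-treatment change share the Visit 2 scan, so its error enters them with opposite signs. With q = s/e, the correlation between the two observed changes is

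rho = (p·q² − 1) / (q² + 2).

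- Adjusting for run-in growth multiplies the variance of the treatment estimate by about 1 − rho²: 1.00 at rho = 0, 0.91 at 0.3, 0.75 at 0.5, 0.51 at 0.7.
- Two covariates at N = 64 cost a further factor of about 61/59 = 1.034.

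**Assumed inputs.** The document gives none of s, e or p. The ranges used are s 1.5–3%, e 1–2%, p 0.8–1.0. The simulated column is the variance of the ANCOVA estimate (log TKV at Visit 8 on treatment and log TKV at Visits 2 and 1) divided by that of the unadjusted change score, from 3,000 replicates.

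| s | e | p | rho | 1 − rho² | × 1.034 | Simulated ratio | 32 ÷ ratio |
|---|---|---|---|---|---|---|---|
| 1.5% | 2% | 1 | −0.17 | 0.97 | 1.00 | 1.02 | 31 |
| 2% | 2% | 1 | 0.00 | 1.00 | 1.03 | 1.04 | 31 |
| 2% | 1% | 0.8 | 0.37 | 0.87 | 0.90 | 0.90 | 36 |
| 2% | 1% | 1 | 0.50 | 0.75 | 0.78 | 0.75 | 43 |
| 3% | 1% | 0.8 | 0.56 | 0.68 | 0.71 | 0.72 | 44 |
| 3% | 1% | 1 | 0.73 | 0.47 | 0.49 | 0.49 | 65 |

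The last column is the number per arm that an unadjusted analysis would need to match 32 per arm adjusted. A repeat with 6,000 replicates gave 1.02, 1.03, 0.90, 0.79, 0.72 and 0.50. Adding site changed each ratio by less than 0.01.

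**Would the repeated-measures ANOVA recover the gain?** Two routes were checked.

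- Contrasting the arms on the difference between on-treatment and run-in change has variance factor 2(1 − rho): 2.0 at rho = 0, 1.4 at 0.3, 1.0 at 0.5, 0.6 at 0.7. Below rho = 0.5 this is less precise than ignoring Visit 1.
- In simulation with the same kind of inputs, the effect was set so that the change-score t-test has about 80% power. The three-visit group-by-time test had 48–73% power, the group main effect about 5%, and ANCOVA on both earlier TKVs 78–98%.

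Using Visit 1 as a response is therefore not equivalent to using it as a covariate.

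**The case against.** Three stronger readings are tempting, and the document supports none of them.

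- **A reader might infer that the plan discards the Visit 1 scan.** It does not say so. The endpoint definition covers all three scans, and the repeated-measures model could include Visit 1. What can be said is that no named method uses it as a covariate, and that the way it enters is not stated.
- **A reader might infer that efficacy on TKV will be judged by before/after tests within each arm**, given the stated purpose of the scans and the naming of a signed-rank test, which is a paired procedure. No within-arm TKV efficacy test is stated, and the independent t-test compares arms.
- **A reader might infer bias from chance imbalance in prior growth.** Under 1:1 randomisation the unadjusted comparison is unbiased, and such imbalance is already reflected in its standard error.

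The best remaining defence is that covariates for a secondary outcome belong in the SAP, and that the gain could be nil. Both parts have force. The SAP may settle the matter, and at q = 1 with full persistence the correlation is zero and adjustment costs a little. But the article does more than stay silent: it names methods, and those methods either leave Visit 1 out or use it as a response. A better method is available from data already scheduled, with a small downside.

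**Conclusion.** The point holds as one of precision on a secondary outcome. It affects neither the validity of the randomised comparison nor the sample size. The named analyses include no covariate, and the role of run-in growth in the between-arm TKV comparison is unstated.

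The size cannot be derived from the document. Under the assumed ranges at 32 per arm, ANCOVA changes the variance by a factor between about 1.04 and about 0.49. The figure of 0.75, worth about 43 rather than 32 per arm, needs scan error at half the growth SD and full persistence; at persistence 0.8 with the same SDs it is 0.90. These figures rest on independent scan errors and on values of s, e and p that the trial's own data would have to confirm. The change is worth making, but the trial does not depend on it.

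**What to change.** Specify in the SAP, before database lock, that the between-arm TKV analysis is an ANCOVA on log TKV at Visit 8 with treatment, log TKV at Visit 2, log TKV at Visit 1 and site. Report the back-transformed treatment coefficient, with its 95% confidence interval, as the ratio between arms of Visit 8 TKV given the earlier values, which expresses the difference in 24-week percentage growth. Enter both earlier TKVs, not the run-in change alone, so that the model can handle the Visit 2 error shared by the two changes. State that this replaces the t-test, Wilcoxon test and repeated-measures ANOVA as the TKV comparison. If the SAP already says this, no change is needed.

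Cost: a sentence or two of text, and no new scan, visit or patient. The model uses four degrees of freedom beyond the unadjusted comparison, two for the TKV covariates and two for the three sites. In the two simulated settings where scan error equalled or exceeded the growth SD, variance rose by 2–4%.

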# The blood test assesses the red blood cell count, white blood cell count, hemoglobin level, and platelet level

*eGFR* estimated glomerular filtration rate, *hCG* human chorionic gonadotrophin, *Scr* serum creatinine, *BUN* blood urea nitrogen, *β2-MG* β2-microglobulin, *mALB/Cr* microalbumin/creatinine, *MRI* magnetic resonance imaging, *RBP* retinol-binding protein, *ALT* alanine aminotransaminase, *AST* aspartate aminotransaminase, *γ-GT* gamma glutamyl transpeptidase, *TCM* traditional Chinese medicine, *TKV* total kidney volume

### Outcomes

The primary outcome of this trial will be the eGFR using the CKD Epidemiology Collaboration formula [21]. Secondary outcomes include changes in TKV, Scr, blood urea nitrogen (BUN), TCM symptoms, and pain. A composite outcome looks at the incidence rates of all possible safety events between two groups. AEs will be monitored throughout the trial and several biological indicators (blood and urine tests, electrocardiograms, and liver function test) will also be closely watched.

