### Participant withdrawal criteria

Participants will be withdrawn from the study ifThey violate any of the key inclusion or exclusion criteria.They refuse to continue to participate or withdraw their consent.They undergo a serious adverse event (SAE).They have unbearable ADPKD-related pain and choose cyst decompression as a surgical intervention during the study.The principal investigator or co-investigators judge that they need to be withdrawn from the study.A hepatocellular injury is detected, indicated by alanine transaminase (ALT) or aspartate transaminase (AST) levels > 3 × ULN and total bilirubin > 2 × ULN, where ULN is the upper limit of normal.They have hematuria during treatment.

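### Scheduled liver tests fit the liver-injury withdrawal criterion poorly: one panel between first dose and the end-of-treatment visit, and no total bilirubin in it

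*Protocol article*

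**What the plan says.** Three parts of the protocol article bear on this point.

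- **Outcomes.** After the efficacy outcomes and the safety composite, the text adds that "several biological indicators (blood and urine tests, electrocardiograms, and liver function test) will also be closely watched". It gives no frequency.
- **Participant withdrawal criteria.** One ground for withdrawal is "A hepatocellular injury is detected, indicated by alanine transaminase (ALT) or aspartate transaminase (AST) levels" above 3 × ULN, combined with total bilirubin above 2 × ULN. Both parts must be met.
- **Table 2 (Measurement items and time points of data collection).** The row "Liver function (ALT, AST, γ-GT") is marked at Visits 1, 2, 5, 8 and 9. The blood-test row has the same marks, and its footnote says: "The blood test assesses the red blood cell count, white blood cell count, hemoglobin level, and platelet level". The row "Electrocardiogram" is marked at Visits 1, 2, 8 and 9. The row "Renal function (eGFR, Scr, BUN") is marked at all nine visits, as are urine tests and vital signs. The row "Drug distribution" runs from Visit 2 to Visit 7.

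The Intervention section gives "YNF as an oral dose of 36 g twice daily 1 h after breakfast and dinner for 24 weeks", so treatment runs from Visit 2 (week 0) to Visit 8 (week 24).

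**The concern.** A biochemical withdrawal criterion protects a participant only if someone measures the relevant analytes while there is still drug to stop. Here participants attend every 4 weeks on treatment and have blood taken for renal function each time. Liver enzymes are scheduled at only one of the five visits between first dose and week 24. The Visit 8 panel arrives when no more drug is being handed out. The Outcomes wording would lead a reader to expect more.

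The liver matters by the protocol's own account. Hepatic disease appears in both the inclusion and the exclusion criteria, and a numerical liver threshold is fixed for withdrawal. The trial is also meant to evaluate the safety of a 17-herb product. At stake are how promptly a symptom-free liver signal would be acted on, and how well a transient enzyme rise would be recorded for either arm.

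**Working it through.** **Inputs.** Visit weeks and marked cells come from Table 2, treatment duration from Intervention, the criterion from Participant withdrawal criteria, and the 72 participants from Sample size calculation. The protocol states no figure for detection delay, so there is none to reproduce.

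**Step 1: count scheduled tests strictly between week 0 and week 24.**

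| Table 2 row | Weeks marked | Strictly between 0 and 24 |
|---|---|---|
| Liver function | −24, 0, 12, 24, 48 | 1 (week 12) |
| Blood count | −24, 0, 12, 24, 48 | 1 (week 12) |
| ECG | −24, 0, 24, 48 | 0 |
| Urine test | all nine | 5 (weeks 4, 8, 12, 16, 20) |
| Renal function | all nine | 5 (weeks 4, 8, 12, 16, 20) |
| Drug distribution | 0, 4, 8, 12, 16, 20 | – |

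The 3-day visit window changes none of these counts.

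**Step 2: which scheduled liver result can shorten exposure?** Week 0 precedes treatment, and week 24 and week 48 come at its end or later. That leaves week 12.

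**Step 3: can the criterion be completed from that result?** It needs (ALT or AST) and total bilirubin. The liver row lists ALT, AST and γ-GT, and the blood test is a cell count only. No other row of Table 2 names bilirubin. From the listed tests, the criterion cannot be completed at any visit, including week 12.

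**Step 4: delay to the next scheduled liver test.** This step makes four assumptions: onset is uniform over the 24 weeks, the abnormality lasts until the next test, results are immediate, and only scheduled tests detect it. Within an interval of length L the mean wait is L/2 and the maximum is L.

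- As scheduled (tests at weeks 12 and 24): L = 12, mean 12/2 = 6 weeks, maximum 12. Onsets followed by a scheduled test before week 24: 12/24 = 50%.
- If read at every 4-weekly visit (comparison only): L = 4, mean 4/2 = 2 weeks, maximum 4. Onsets followed by a scheduled test before week 24: 20/24 = 83%.

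**Range without the uniform assumption.** The wait can lie anywhere from 0 to 12 weeks as scheduled, and from 0 to 4 weeks under 4-weekly reading. The 50% becomes 100% if every onset falls before week 12, and 0% if every onset falls after it. The 83% likewise runs from 100% (all onsets before week 20) to 0% (all after it). The documents give no onset distribution. The 12-week spacing and the single usable visit do not depend on one.

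**Step 5: number of added panels if the four empty on-treatment cells were used.** 72 × 4 = 288 at most, if every randomized participant attends Visits 3, 4, 6 and 7.

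**The case against.** The best defence is that nothing here is a numerical contradiction. Close watching is not a frequency, and Table 2 supplies the frequency. The criterion applies whenever injury is detected and is not tied to scheduled panels. Adverse events are assessed at Visits 3 to 8, each is followed until it resolves, and investigators may withdraw a participant on judgement. Patients with liver disease are excluded, and the Discussion describes adverse effects as mild, with no safety concern raised in practice. All of this stands, and it limits the claim to scheduled tests. It does not help with a rise that causes no symptoms, and a record of clinical use does not replace measurement in a trial meant to assess safety.

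A reader might go further and infer four things that the documents do not support:

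- **That the withdrawal criterion is inoperative, or that injury after week 12 cannot be found in time.** Event-prompted testing is not excluded, so this does not follow.
- **That half of liver injuries would be missed.** The 50% holds only for scheduled tests under uniform onset.
- **That the sparse blood counts and ECGs also disable a stopping rule.** No withdrawal criterion uses either. A heart rate below 40 bpm, listed as a safety event, can be seen from vital signs, taken at every visit. Urine tests, named in the same Outcomes sentence, are done at every visit. The blood-count and ECG gaps concern wording only.
- **That the between-arm safety comparison is biased.** Both arms share one schedule. Sparse testing lowers sensitivity to transient rises but does not by itself favour an arm, and the listed safety events do not name isolated enzyme rises.

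**Conclusion.** The point holds in limited form. The plan sets a liver-injury criterion and describes close observation. Its own schedule offers one liver panel at which a result could shorten exposure, and that panel omits an analyte the criterion requires. These two facts come straight from Table 2 and the withdrawal criteria and need no modelling.

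The size is a 12-week gap between scheduled liver tests on treatment. The mean wait is 6 weeks, against 2 weeks at the existing 4-weekly visits, under the assumptions of Step 4. The mismatch with the Outcomes sentence is one of wording against schedule. The primary eGFR analysis and the sample size are unaffected. This deserves correction because the remedy is cheap, not because the documents show harm.

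**What to change.** Reconcile Table 2, the liver-injury item in Participant withdrawal criteria and the Outcomes sentence, so that the analytes and timing of scheduled liver tests let the criterion operate during treatment. Two matters need settling:

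- **Analytes.** The scheduled panel and the criterion must refer to the same measurements. At present total bilirubin is in one and not in the other.
- **Timing.** The clinical team sets the frequency; no particular interval is proposed here. Blood is already drawn for renal function at Visits 3, 4, 6 and 7, so tests could be added without a new visit. Whether those samples suffice for a liver panel is for the laboratories to confirm.

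If the schedule is kept, the Outcomes section should say that liver function and blood counts are checked once, and ECG not at all, between first dose and the end-of-treatment visit. It could also say that event-prompted testing is possible, if that is intended.

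The cost is a short edit to the text or to one row of Table 2, and at most 288 extra panels if all four visits were used. Keeping the schedule and correcting the wording adds no liver panels.
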